## Abstract

**Background:**

Individualized treatment for commercial tobacco smoking cessation, such as through the utilization of the nicotine metabolite ratio (NMR), offers substantial clinical benefit. NMR is a metabolism-informed biomarker that can be used to guide medication selection. NMR testing is particularly promising for tobacco cessation efforts in populations with high rates of smoking, such as some Alaska Native and American Indian (AN/AI) communities. To date, no prior study has evaluated the implementation of NMR-guided tobacco cessation with AN/AI populations.

**Methods:**

The present “QUIT” protocol is a two-phase study that will occur at Southcentral Foundation (SCF), an Alaska Native-owned health system, serving 70,000 AN/AI people, based in Anchorage, Alaska. In Phase one, qualitative interviews with customer-owners (patients), providers and administrators (n = 36) and a 10-participant beta-test will be used to refine a strategy to implement NMR testing in the health system. Phase two will involve a single-arm pilot trial (n = 50) and qualitative interviews throughout data collection (n = 48) to evaluate the implementation strategy and explore the real-world acceptability and feasibility of NMR testing to guide tobacco cessation with AN/AI populations.

**Discussion:**

This study utilizes a community-based participatory approach to refine and implement a nicotine metabolism-informed smoking cessation program in a Tribal healthcare setting. The process and findings from this study will reflect the importance of customer-owner choice and honor the lived experience involved in quitting commercial tobacco. Pilot study data will inform the effect and sample sizes required for a future pragmatic trial of NMR-guided smoking cessation.

## Introduction

In Alaska, two-thirds of people who smoke commercial tobacco want to quit, and more than half of these individuals have tried to quit in the last year.^1^ Although there have been considerable advances in healthcare for American Indian and Alaska Native (AI/AN) peoples in recent decades,^2^ improving smoking cessation treatment remains an important priority in addressing health disparities. The prevalence of smoking among adults in the U.S. dropped from 95% in 1980 to 14% in 2020. Among the AI/AN population, however, rates remain among the highest in the nation at 23%. Furthermore, tobacco-related mortality is 60% higher among AI/AN people than white people in the U.S..^3^ Although the estimated number of people with tobacco-related health problems has gradually declined, there continues to be 60% higher smoking-attributable mortality (e.g., lung cancer, COPD, heart disease, and stroke) among AI/AN persons than among white people^3^, and quit rates are lower for AI/AN adults than others.^1^

Nicotine replacement therapy (NRT) remains the most frequently used first-line pharmacologic treatment for tobacco cessation.^4^ While several medications are currently available for tobacco cessation, including NRT, varenicline, and bupropion, selecting the most effective medication for an individual can be a lengthy process and include serious side effects. Nicotine metabolism can be affected by many things including environmental factors and genetic variations, specifically in the CYP2A6 allele.^5^ The nicotine metabolite ratio (NMR) is a genetic test that reveals how a person metabolizes nicotine and holds promise for identifying the most effective tobacco cessation medication with the fewest side effects.^6, 7^ The NMR biomarker identifies how “slow” or “fast” a person clears nicotine. For example, individuals with slow nicotine metabolism have been found to respond well to treatment with NRT, but individuals with normal or “fast” nicotine metabolism are significantly more likely to be successful in quitting tobacco using varenicline.^7^

Wells et al.^8^ demonstrated the feasibility of a metabolism-informed care process using ad hoc NMR testing to increase NMR-treatment match rates. Participants were informed by a nurse tobacco specialist of optimal smoking cessation treatments and encouraged to follow NMR-informed recommendations. They found that participants who were randomized to the metabolism-informed care group had higher medication matching (84%) compared to the usual-care group (58%).

A recent observational study of AI/AN adults starting the Quit Tobacco Program (QTP) at Southcentral Foundation found that 28% of participants demonstrated slow nicotine metabolism (NMR < 0.31), 66% had normal nicotine metabolism (NMR ≥ 0.31), and 6% had an NMR that was unquantifiable (either cotinine or 3-hydroxycontinine values were < 1.5 ng/mL at baseline).^9^ Of the total sample, 24% were smoking-abstinent at six weeks. A combined group of people with slow metabolism who used NRT and people with normal metabolism who used varenicline had a quit rate of 36.5%, a 13% higher quit rate than in the total sample. However in retrospective analyses, only 37% of participants chose a treatment that matched NMR-informed recommendations because no process was in place to inform them of the optimal treatment.^10^

The present study protocol aims to: 1) adapt a protocol to implement NMR testing for pharmacologic tobacco cessation treatment by conducting qualitative interviews with potential end users and stakeholders followed by a beta-test; and 2) conduct a single-arm pilot trial to assess the acceptability and feasibility of the intervention including evaluation of factors which may facilitate or impede the implementation of the intervention within the Alaska Tribal Health System (ATHS). We expect that establishing a culturally respectful testing process with customer-owners, and a logistically feasible clinical workflow for providers and leaders will support the implementation of an effective smoking-cessation intervention among AI/AN peoples in a real-world setting.

## Methods

### Study Overview

This study incorporates a Community-Based Participatory Research (CBPR) approach with AI/AN customer-owners, providers, and leaders to assess the acceptability and feasibility of a planned tobacco-cessation intervention.^8^ CBPR is a collaborative research approach that equitably involves community members, researchers, and other stakeholders in the research process and recognizes the unique strengths that each bring.

This mixed-methods study will be conducted in two phases (Fig. 1). Phase 1 is a qualitative study using individual, semi-structured interviews to elicit feedback about the acceptability and feasibility of using NMR to inform selection of pharmacologic treatment followed by a beta-test of the intervention. After refining study procedures in the beta-test, Phase 2 will pilot a single-arm trial and implementation analysis to examine factors which may impede or support implementation of the intervention within the Alaska Native Tribal health system. Our multidisciplinary team includes researchers, including AN/AI community members, with expertise in tobacco-cessation pharmacotherapy, public health, psychology, anthropology, intervention adaptation, community-engagement, and implementation science. We have also involved and appreciated AI/AN persons’ input and participation, including SCF customer-owners (i.e. SCF patients), SCF providers, and tribal health system leaders, in every phase of project development.

### Setting

SCF serves 70,000 AI/AN peoples in the Anchorage and Matanuska-Susitna Boroughs and 55 rural villages. Most study activities will take place in SCF-owned buildings on the Alaska Native Health Campus in Anchorage, Alaska (pop. ~300,000). Customer-owners interested in smoking cessation typically discuss this with their primary care providers before being referred to the Quit Tobacco Program (QTP). SCF has a dedicated department within Health Education called the Quit Tobacco Program (QTP) in which customer-owners can access cessation medications, behavioral counseling, or social support to help stop smoking.

### Regulatory Approvals

Our study was approved by the Alaska Area Institutional Review Board and SCF Research Review Committee.

### Participants

Customer-owner participants will complete some data collection activities at home for convenience. For Phase 1, semi-structured interviews will be conducted with eligible customer owners: AI/AN persons ≥ 18 years of age who are receiving services at SCF and use cigarettes as the main form of tobacco, smoked ≥ 1 cigarette per day over the last 30 days, are willing to make a quit attempt within 30 days of enrollment in the QTP, and have phone service. Six SCF clinical/administrative leaders and six providers will also be interviewed to understand practice needs and inform intervention materials and procedures. Clinic administrators and SCF leaders known to research staff will be emailed recruitment invitations, and the list of leaders will be reviewed by the Research Oversight Committee to ensure balanced workgroup representation.

Eligibility for Phase 2 beta-test customer owner participants will be the same as the Phase 1 interviews, plus having broadband internet connection on a mobile phone at home, work, or other location to complete smoking abstinence measures via phone or video teleconference. Interested individuals will be excluded from the beta-test if they participated in Phase 1 interviews, have participated in a smoking cessation program in the last three months, are contraindicated for the use of varenicline, have bleeding disorders, or are currently receiving cancer treatment. Care team staff eligibility for the beta-test includes being a healthcare professional at SCF and being directly involved in the care of a beta-test participant.

Eligibility for customer-owner participants in the Phase 2 pilot trial matches the beta-test; anyone who participated in an earlier phase of the study will be excluded. Phase 2 implementation interviews will be conducted with pilot trial participants, as well as SCF administrative leaders and clinical providers who have a customer-owner enrolled in the pilot trial.

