### Phase 1 Beta-Test of NMR Implementation Strategy

A sex-stratified, purposive sample of 10 customer-owners will be enrolled in a beta-test of the NMR implementation strategy. The goal of the beta-test will be to refine the implementation strategy before the Phase 2 pilot. Phase 1 beta participants will be recruited through SCF primary care clinics and Quit Tobacco Program (QTP) referrals, word of mouth, and study flyers. Screening will occur by phone or in-person. Confirmation of eligibility and written informed consent will occur in-person or remotely online.

Following enrollment, participants will complete a demographic survey and have a blood sample (< 5ml) drawn prior to an intake with the QTP. Samples will be express shipped to a certified laboratory (Quest Diagnostics lab; Chantilly, VA) for NMR quantification, and results will be entered into the electronic medical record (EMR) and calculated as either slow (< 0.31) or normal (≥ 0.31) nicotine metabolism. Results are expected within 3–6 days of sample arrival at the laboratory. The appropriate therapeutic recommendation will be viewable by the care team in the EMR. Individuals with slow NMR will be recommended NRT patch. Individuals with normal metabolism will be recommended varenicline or bupropion, either alone or in combination with NRT gum or lozenge.

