Although participants will be shown a list of their recommended medications, they will be able to select any of the provider-approved medications for which they are medically eligible. If an individual wishes to start medication immediately before NMR results are available, they will be recommended varenicline or bupropion (the recommendation for normal metabolizers) as NMR normal metabolizers are more common than slow metabolizers. Twelve weeks of medication will be dispensed by pharmacists through the standard clinical procedures, and participants will also have access to the usual non-pharmacologic treatments (e.g., behavioral counseling and support by phone) through the QTP. Six weeks after the participants’ quit date (set by the participant with the QTP), they will complete a follow-up survey and at-home smoking cessation tests to confirm biochemical abstinence. At-home smoking tests will be mailed to participants and will include an Ico Smokerlyzer^®^ (Bedfont Scientific) which will connect wirelessly to their smartphone and a NicAlert^™^ saliva test strip which is a small and inexpensive lateral flow immunoassay test strip that is activated by eight drops of saliva. Also included in the mailed at-home test kits are step-by-step lay language instructions re-written from the original instructions. The test will also include photos of study staff self-administering both tests. Beta-test participants will receive a $50 gift card for the baseline blood draw and $75 for the follow-up study visit.

After customer-owner participants have completed the clinical process of NMR-informed medication recommendation, semi-structured interviews will be conducted with up to 20 care team members (two for each customer-owner participant). Recruitment emails will be sent to staff known to have been involved in the care of beta-test participants, and verbal consent will be obtained prior to the interview. Interviews will not be recorded, but detailed notes will be taken by the interviewer. To accommodate staff schedules, staff participants can complete a survey in place of an interview. Best-test data including demographic, acceptability questions, Electronic Health Record data and follow-up measure results will be analyzed using descriptive statistics. Content analysis will be used to analyze the interview data, brief study notes from the CO beta-test study visits and individual and group staff interviews.

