### Phase 2 Pilot Trial and Implementation Evaluation

Following Phase 1, measures may be modified to reflect the results of the beta test, and a single-arm pilot trial will be conducted with 50 customer-owners to evaluate the refined implementation strategy and explore the effectiveness of the NMR for optimizing individual tobacco cessation treatment. The sample size was determined assuming a 60% retention rate to ensure at least 30 participants have follow-up data at 26 weeks.^13–15^ Follow-up visits will be conducted as follows: at 6 weeks after starting pharmacologic treatment (to assess intervention acceptability, nicotine dependence/withdrawal, side effects, and medication adherence); at 12 weeks, the planned end of pharmacologic treatment (to assess all 6-week measures plus acceptance of study processes and biochemically verified quit status); and at 26 weeks (to assess biochemically verified quit status). Pilot-trial participants will receive the same compensation as beta-test participants for completing study procedures.

Phase 2 will also explore barriers and facilitators to implementation of the intervention within SCF to prepare for a future pragmatic trial. At the mid-point and end of the pilot trial (13 and 26 weeks), we will conduct brief, semi-structured interviews with six SCF leaders (e.g., administrators, clinical directors, tribal leaders) and six randomly selected providers who had a customer-owner who participated in the pilot trial. Interviews will assess the process of using metabolism-informed care and challenges in adhering to the treatment recommendations. Brief, semi-structured interviews will also be conducted with 12 trial participants at the mid-point and end of the pilot trial, randomly selected within sex strata, about the intervention and treatment fidelity. Trial participants will be paid $25 per interview for a total of up to $50, but SCF staff will not receive additional compensation because interviews will be conducted during paid working hours.

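### No biochemical confirmation of smoking is listed at entry, so a few participants who already test negative could count as verified quitters in the exploratory abstinence rate.

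*Protocol article*

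**What the plan says.** **Entry.** The Participants section requires cigarettes as the main form of tobacco and that the person "smoked ≥ 1 cigarette per day over the last 30 days". This is set out for the Phase 1 interviews, and the beta-test takes it over. The pilot follows: "Eligibility for customer-owner participants in the Phase 2 pilot trial matches the beta-test". No biochemical test is listed as a condition of entry. For the beta-test, "Screening will occur by phone or in-person", and eligibility may be confirmed remotely.

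**Baseline sample.** Blood is taken only after entry: "Following enrollment, participants will complete a demographic survey and have a blood sample (< 5ml) drawn prior to an intake with the QTP". Its stated purpose is to classify nicotine metabolism as slow or normal. Table 3 counts participants with a quantifiable NMR result, as a feasibility measure.

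**Follow-up.** In the beta-test, six weeks after the quit date, "they will complete a follow-up survey and at-home smoking cessation tests to confirm biochemical abstinence"; the tests are a home breath CO device and a saliva strip. In the pilot, verified quit status is assessed at 12 weeks "and at 26 weeks (to assess biochemically verified quit status").

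**Use.** Under Outcomes and Statistical Methods, the primary outcomes are acceptability and feasibility and every analysis is exploratory. Abstinence is compared across follow-up visits, and the pilot data are to supply an effect size and sample size for a pragmatic trial.

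**Site evidence.** The Introduction reports for the earlier observational study that "6% had an NMR that was unquantifiable (either cotinine or 3-hydroxycontinine values were < 1.5 ng/mL at baseline"), and also: "Of the total sample, 24% were smoking-abstinent at six weeks".

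**The concern.** A biochemical test at follow-up shows that someone stopped only if that person would have failed it at the start. Here the smoking floor at entry is low, apparently taken on the participant's word, and not paired with a baseline test. The site's own data show that some people entering this programme had a marker below the assay limit. If such a person reports abstinence later, the test cannot contradict the report, and nothing in the article removes or marks that person in the quit rate.

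These people also fall outside the intervention's logic. The article defines a recommendation for slow and for normal metabolism, not for an unquantifiable result, so an NMR-guided choice cannot explain their abstinence.

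What is at stake is the exploratory quit rate at 12 and 26 weeks and the effect size drawn from it. The error can only push the rate up, and a larger sample in the next trial would not average it out.

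**Working it through.** **The plan's own figure.** 30 participants with 26-week data at 60% retention: 30 / 0.60 = 50. This reproduces the stated sample size. The article gives no power calculation to check.

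**Inputs**
- n = 50 enrolled, 30 retained at 26 weeks (Phase 2 Pilot Trial section).
- Illustrative quit rate in the others: p = 24%, the six-week figure in the Introduction.
- f = share who already test negative at entry and are counted as quit. The article does not give f. The 6% with unquantifiable NMR is a proxy; the low end is 0.

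**Number affected.** Expected number = n × f.
- f = 0: none.
- f = 6%: 50 × 0.06 = 3 enrolled, or 30 × 0.06 = 1.8 retained.
- Chance of at least one at f = 6%: 1 − 0.94^50 = 0.955 among 50; 1 − 0.94^30 = 0.844 among 30.

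**Effect on the rate.** Observed rate = f + (1 − f) × p.

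| f | Observed rate if 24% in the others |
|---|---|
| 0 | 24.0% |
| 2% (assumed) | 0.02 + 0.98 × 0.24 = 25.5% |
| 6% (all unquantifiable) | 0.06 + 0.94 × 0.24 = 28.6% |

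The largest shift that the 6% supports is 28.6 − 24.0 = 4.6 points.

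**Against sampling error.** 95% half-width = 1.96 × √(p(1 − p)/n).
- n = 50: 1.96 × √(0.24 × 0.76 / 50) = ±11.8 points.
- n = 30: 1.96 × √(0.24 × 0.76 / 30) = ±15.3 points.

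The shift is well inside both.

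**How sound is the 6% as a proxy?** It counts people with either analyte below the limit. Low 3-hydroxycotinine alone is compatible with measurable cotinine and active smoking, so the share with low cotinine may be anywhere from near 0 to 6%. In the other direction, the article gives no cut-off for the breath or saliva test. Light smokers above 1.5 ng/mL might also test negative, and the article offers no figure with which to size that group.

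**The case against.** The strongest reply is that nothing primary is affected. The Discussion says that efficacy is not the primary endpoint and that pharmacologic efficacy will not be formally analysed. That stands. A reader might infer that verified quit status is the trial's outcome and that its main result is compromised; the article says otherwise.

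Second, this is a condensed article. Cut-offs, the abstinence definition and analysis sets are commonly left to the full protocol, and a low smoking floor suits a real-world implementation study. This also stands in part: the floor is not an error, a baseline check may exist elsewhere, and self-report is inferred from the wording and the phone screening. With no cut-off given, one cannot say that the entry floor lies close to the response threshold. What remains is what the article itself sets down: a low floor, blood drawn after enrolment, verified outcomes later, and a site figure showing that low markers at entry do occur.

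Third, a negative test at entry does not by itself make a quitter. The person must also complete follow-up and report abstinence, and a light smoker who truly stops is a genuine success. This is right, and it is why 3 of 50 is the high end.

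Fourth, a reader might infer that the earlier study's 24% was itself inflated. The Introduction does not say whether people with unquantifiable NMR were among the abstinent, or that the 24% was biochemically verified, so no corrected figure can be derived.

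Finally, people negative throughout would add about equally at each visit, so the comparison between visits changes little. The level of the rate is what moves.

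**Conclusion.** The point holds as a modest one. The entry criteria and the verified follow-up outcome, as listed, allow a person already negative at entry to be counted as a quitter. By the article's own site figure this concerns 0 to about 3 of 50 participants, and raises a 24% rate to at most 28.6%. That ceiling assumes that every unquantifiable result means a negative follow-up test, that all these people are counted as quit, that follow-up is equally complete in both groups, and that the earlier study's entrants resemble the pilot's. It covers only the group behind the 6%.

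The shift is smaller than the pilot's sampling error and leaves acceptability and feasibility alone. It deserves attention because it is one-directional, enters a stated planning input, and can be removed with data the trial collects anyway.

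It would go too far to conclude that the pragmatic trial must be planned from confirmed smokers alone. That trial may enrol under the same broad criteria, and the earlier 24% refers to a total sample that includes the unquantifiable 6%. Which figure is the right comparator depends on the design of that trial, so both are needed.

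**What to change.** Add a sentence to Outcomes and Statistical Methods along these lines: participants negative at entry will be flagged from the baseline NMR assay, and abstinence at 12 and 26 weeks will be reported for all enrolled and again excluding those flagged.

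- **Flag.** Use the baseline cotinine value, against a limit stated in advance, if the laboratory reports it. The article mentions only NMR results in the medical record, so this must be checked. Otherwise use unquantifiable NMR, which follows from the count already in Table 3. This is a blunter flag, because it also catches people with low 3-hydroxycotinine alone.
- **Planning.** Show both rates when the effect size for the pragmatic trial is estimated.
- **Primary outcomes.** Keep everyone in the acceptability and feasibility measures.

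The cost is one sentence and one derived variable, with no new test and no change to eligibility. The second figure will rest on a slightly smaller denominator (about 47 to 50 of the 50 enrolled) and may show a slightly lower quit rate.
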